#### Intervention description {11a}

The intervention would be performed for 24 weeks, the 1–12 weeks are double-blinded, and the 13–24 weeks are open-labeled. The volume of renal calculi is slowly decreases and 24 weeks may be needed, while this will lead to the increasing rate of shedding, so the 13–24 weeks are open-labeled.

(1) Sodium bicarbonate group: sodium bicarbonate (1 g tid) will be performed for 24 weeks.

(2) Placebo group: the placebo will be performed for 12 weeks and not be performed from 13 weeks to 24 weeks.

(3) Both groups are administered febuxostat (40 mg/day) for 24 weeks.

(4) Drugs to prevent gout flares: prednisone acetate (5 mg Qd), celecoxib, or colchicine (12 weeks).

(5) During this trial, all subjects will receive general treatment, including ① strict diet: intake of low-calorie diet to maintain ideal body weight. Avoid food with high purine content, such as animal offal, thick gravy soup, sardines, and clams, oysters. The moderate consumption of fish, shrimp, meat, and pea with a moderate amount of purine. The daily diet consists of low purine content of cereal products, fruits, vegetables, milk, dairy products, and eggs. Also, drinking >2000 mL of water every day and give up all kinds of alcohol strictly. ② Avoid inducements including smoking, overeating, cold, dampness, overfatigue, and stress. In addition, it is necessary to slip into comfortable shoes, prevent damage of joint, and only sparingly use drugs that seriously affect uric acid excretion (such as some diuretics). ③ Concomitant disease control: concurrent treatment of concomitant hyperlipidemia, diabetes, hypertension, coronary heart disease, and cerebrovascular disease.

#### Research procedures

(1) Screening: In line with 2015 ACR and EULAR criteria and the score system for acute arthritis of gout, B ultrasonography suggests renal calculi. The patients are 18–80 years old.

(2) Enrolment: Each subject will be interviewed by investigators prior to the start of the treatment, and the data would be input into the database along with baseline data. The subjects will be divided into test and control groups according to the treatment, and both groups will be treated for 6 months. Renal calculus volume changes before and after treatment will be observed and recorded, respectively.

(3) Treatment scheme: Test group: sodium bicarbonate 1 g tid combined with febuxostat 40 mg/day and prednisone acetate 5 mg Qd for 12 weeks. Control group: placebo 1 g tid combined with febuxostat 40 mg/day and prednisone acetate 5 mg Qd for 12 weeks.

(4) Laboratory indicators: Vital signs (pulse, blood pressure, temperature, respiration, and gout flares), four physiological indicators of blood lipids (TC, TG, HDL-C, LDL-C), fasting blood glucose, blood routine (RBC, WBC, NEUT, PLT, Hb), urine routine (pH value of urine, PRO, BLD), renal function (BUN, CREA, sUA, EGFR), liver function (ALT, AST, GGT, ALP), erythrocyte sedimentation rate (ESR), C-reactive protein (CRP), and renal DECT (location, size, quantity component of renal calculi).

#### Criteria for discontinuing or modifying allocated interventions {11b}

Rejection criteria

(1) The combination of drugs violates the protocol, or patients fail to use drugs in accordance with the provision, which in turn affects the outcomes.

(2) Incomplete data affecting the efficacy and the judgment of safety.

Shedding criteria

(1) Serious adverse reactions related to the study drug.

(2) In this study, major mistakes are detected in the clinical research protocol, which makes it difficult to evaluate the efficacy of the drug. Also, a significant deviation is observed in the implementation of a well-designed protocol.

Subject termination criteria

(1) Subject terminates spontaneously (for example, withdrawal of the informed consent).

(2) Subject is pregnant (must drop out of the study).

(3) Subject uses a combination of drugs within a non-prescribed range, which affects the judgment of efficacy and safety.

(4) Indicators of liver function: transaminase ≥3 times the upper limit of normality for more than 1 week.

(5) Adverse events that prompts the investigator to decide that the subject has to quit early.

(6) Compliance of the subject with the research protocol is poor, and the quantity of medication is not between 80% and 120%.

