#### Sample size {14}

This is a differential test, and the primary outcome is the proportion of patients whose renal calculus volume is reduced after 3 months of treatment. A test level with a two-sided *P* value of 0.05 and a power of 80% is assumed, and the ratio of patients’ number in the sodium bicarbonate to the placebo group was 1:1. The parameters of preliminary studies have demonstrated that the reduction rate of renal calculus volume in the test group is 89.74% in 3 months and 64.10% in the control group. The estimated sample size will be 42 in the trial group and 84 in the control group. In this study, the shedding rate does not exceed 15%, and the sample size for each group is determined to be 49.

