#### Methods in the analysis to handle protocol non-adherence and any statistical methods to handle missing data {20c}

Study populations include the intent-to-treat (ITT) analysis set defined as all randomized patients, and the per-protocol (PP) analysis set defined as all patients in the ITT population without any major protocol deviations. Multiple imputation is used to manage missing values.

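### The rejection and termination rules in {11b} conflict with, or leave open, the all-randomised ITT set and multiple imputation in {20c}

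*Protocol article*

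**What the plan says.** Section {11b} of the protocol article has three lists.

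- The rejection list covers drug combinations that violate the protocol, cases where "patients fail to use drugs in accordance with the provision, which in turn affects the outcomes", and "Incomplete data affecting the efficacy and the judgment of safety".
- The shedding list includes serious reactions related to the study drug.
- The termination list includes withdrawal of consent, pregnancy, adverse events that lead the investigator to take the subject out, and the case where "Compliance of the subject with the research protocol is poor, and the quantity of medication is not between 80% and 120" per cent.

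The section does not define rejection, does not say which analysis a rejected patient leaves, and does not say whether a terminated patient is still assessed at week 12.

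Section {20c} sets out the analysis populations: "the intent-to-treat (ITT) analysis set defined as all randomized patients", and a per-protocol set of ITT patients free of major deviations. Missing values are to be multiply imputed.

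Section {14} plans 42 patients per group and raises this to 49 for shedding of at most 15%.

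**The concern.** Incomplete data cannot be a reason to stop giving a drug. Although {11b} is headed as a section on changing the allocated intervention, that line only makes sense as a rule for leaving a patient out of the data. It then collides with {20c}: if such patients are rejected there is little left to impute, and if they are imputed they have not been rejected.

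The adherence lines are less clear-cut but raise the same risk. Whether wrong drug use affected the outcome is judged after randomisation. The 80–120% rule ends a subject's participation, and no text keeps that subject in for the primary outcome measurement.

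These exits may be related to treatment. The adverse-event section {22} expects gastrointestinal symptoms with sodium bicarbonate, and the Discussion says that adverse reactions to alkalizing drugs lead to poor compliance. If such patients drop out of a comparison of 49 per arm, the balance that randomisation gives is no longer assured.

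**Working it through.** **Setting the sections side by side**

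| Rule in {11b} | Position in {20c} | Compatible? |
|---|---|---|
| Incomplete data: rejected | All randomised patients in ITT; missing values imputed | No, if rejection means leaving the analysis, which is the only natural reading |
| Drug use that affects outcomes: rejected | Stays in ITT; may be a major deviation for PP | Only if rejection means PP exclusion or stopping treatment; not stated |
| Intake outside 80–120%: terminated | Stays in ITT | Only if outcome data are still collected or imputed; collection not stated |

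**The plan's own figure.** Inputs from {14}: two-sided alpha 0.05; "a power of 80% is assumed"; "the reduction rate of renal calculus volume in the test group is 89.74% in 3 months and 64.10% in the control group"; allocation 1:1.

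Pooled-variance formula: n = [1.96·√(2·p̄(1−p̄)) + 0.8416·√(p1(1−p1) + p2(1−p2))]² / (p1−p2)², with p1 = 0.8974, p2 = 0.6410, p̄ = 0.7692.

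- Numerator: (1.96 × 0.5959 + 0.8416 × 0.5676)² = 2.708
- Denominator: 0.2564² = 0.0657
- n = 41.2, so 42 per group. The stated 42 is reproduced. The 84 given for the control group fits only as the total under 1:1.

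For shedding, 42 × 1.15 = 48.3, so 49; 42/0.85 = 49.4. In reverse, 49 × 0.85 = 41.7, about the 42 needed. The sample size is therefore planned as if shed patients give no primary outcome. Power is 80.8% with 42 per group and 86.5% with all 49.

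**Illustration of what exclusion could do.** The documents give no loss rate by arm and no response rate in those lost, so every input below except 64.1% is assumed. Suppose there is no true effect (64.1% in both arms) and a fraction r of the bicarbonate arm only is removed, responding at rate q. The retained rate is (0.641 − r·q)/(1 − r), and the spurious gain is r(0.641 − q)/(1 − r).

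| r | q | Spurious gain |
|---|---|---|
| 10% | 45% | 0.10 × 0.191/0.90 = 2.1 points |
| 10% | 30% | 0.10 × 0.341/0.90 = 3.8 points |
| 15% | 45% | 0.15 × 0.191/0.85 = 3.4 points |
| 15% | 30% | 0.15 × 0.341/0.85 = 6.0 points |
| any | 64.1% | 0 |

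At q = 40%, the nominal 5% test rejects in 5.8% of trials with r = 10% and in 7.0% with r = 15%.

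If both arms lose patients, say 15% on bicarbonate and 10% on placebo, all responding at 40%, the retained rates are 68.4% and 66.8%. The gain is then 1.6 points, against 4.3 for the one-sided 15% loss.

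**The case against.** The strongest reply is that {11b} concerns treatment and {20c} concerns analysis. Section {20c} already states the right ITT definition and gives non-adherent patients a place through the PP set, and no sentence says that rejected, shed or terminated patients leave ITT. For the adherence lines this stands: a reading compatible with {20c} exists. It does not rescue the incomplete-data line.

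Several stronger readings are tempting but not supported:

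- A reader might infer that the rules remove bicarbonate-intolerant patients and so favour bicarbonate. The criteria apply to both arms, both arms take several medicines, {22} describes treatment for gastrointestinal effects, and decisions up to week 12 are blinded. Blinding does not stop a drug's own effects from driving adherence, so a treatment-related loss is plausible, but no more than that.
- A reader might infer that terminated patients have no week-12 DECT. The text is silent. The 15% allowance shows that loss was planned for, not that scans are withheld.
- A reader might object that imputation under missing-at-random would fail here. The protocol does not state that assumption, and imputation details may properly sit in a SAP that is not shown.
- A reader might take 15% as the loss in the active arm. It is an overall ceiling.

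That {20c} does not name the primary set is likewise no fault by itself, as a SAP may do so. The finding is that two sections of this document give different instructions about the same patients.

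**Conclusion.** The point holds in limited form. Rejection for incomplete data contradicts an all-randomised ITT set with multiple imputation. The outcome-linked non-adherence rule and the 80–120% rule are ambiguous: followed literally, they could produce post-randomisation exclusions, and the shedding allowance in {14} already treats shed patients as lost to the primary outcome.

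The documents do not establish that bias will occur, nor its direction or size. The 2–6 points rest wholly on assumed one-sided loss of 10–15% and an assumed response of 30–45% in those lost. The matter is worth settling while patients are being followed, because a week-12 scan that was not taken cannot be recovered.

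**What to change.** Reconcile {11b} and {20c}:

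1. Delete incomplete data as a rejection reason.
2. State that rejection, shedding or termination removes no one from the ITT set.
3. State that, for analysis, non-adherence (including the 80–120% criterion) serves only to define the PP set.
4. Name ITT as the primary analysis and PP as a sensitivity analysis.
5. Separate stopping study drug from leaving the study. Obtain the week-12 DECT, which the primary outcome already needs, after study-drug discontinuation, unless consent is withdrawn or the protocol's own safety rules require the patient to leave.

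No clinical stopping rule changes.

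The cost is protocol wording, a few scans in patients off study drug, and possibly a smaller effect estimate. For scale, assume that the 89.74% in {14} applies to patients who stay on treatment (which {14} does not say) and that 15% of the bicarbonate arm responds at the control rate. The all-randomised rate is then 0.85 × 0.8974 + 0.15 × 0.641 = 85.9%, the difference is 21.8 rather than 25.6 points, and power with 49 per arm is 70.8% rather than 86.5%. If those 15% respond at 40%, the difference is 18.2 points.

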#### Strategies to improve adherence to interventions {11c}

We will call the subjects back to the hospital regularly for follow-up, laboratory tests were performed, and subjects were asked to return the drug tablet at each follow-up visit.

#### Relevant concomitant care permitted or prohibited during the trial {11d}

*This* trial will not impose *special requirements for* care and interventions.

#### Provisions for post-trial care {30}

When the trial complete, the subjects will receive standardized treatment based on the guideline.

#### Outcomes {12}

##### Primary outcomes

The proportion of patients whose renal calculus volume is reduced after 12 weeks of treatment.

##### Secondary outcomes

The volume changes of renal calculi, uric acid changes, and the proportion of patients whose sUA levels are <360 μmol/L, the changes in eGFR, the pH value of urine, and adverse effects after 12 and 24 weeks of treatment. Adverse events will be monitored during the 24 weeks of treatment, including the incidence of hypertension before and after treatment, the incidence of post-treatment edema, and the rate of acute gout attack within 12 weeks. Any adverse reactions that occur during the study will be recorded in the “Adverse Reaction Table,” and the patients will be followed up until symptoms disappear or indicators return to normal. In the event of serious adverse events, necessary measures will be taken immediately to ensure the safety of the subjects. In addition to evaluating the primary and secondary outcomes, safety assessment will be conducted at baseline and at 24 weeks after treatment with respect to blood pressure, respiration, heart rate, blood routine, urine routine, liver and renal function, ESR, CRP, and renal DECT.

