Another study suggested that the pH value of urine increased from 5.5 to 6.0 by administering sodium bicarbonate (1 g tid) for 3 months in gout patients [7]. Although several urological associations recommended urine alkalization to promote calculi dissolution in nephrolithiasis [8–11], advanced evidence is lacking. Since alkaline urine may increase the risk of hypertension, water-sodium retention, and heart failure, according to the 2020 American College of Rheumatology (ACR) guideline, starting alkalizing urine is not recommended even in cases of stimulated uric acid excretion. Based on the composition, renal calculus is mainly divided into calcified calculi, urate calculi, cystine calculi, and combinations. Typically, nephrolithiasis is assessed by ultrasonography, plain film radiography, tomography, or excretory urography with an intravenous contrast agent [12]. However, none of these methods could identify calculi before treatment. Dual-energy computed tomography (DECT) is a novel non-invasive technique that fundamentally distinguishes the composition of urate calculi. This method has been previously validated in both in vitro and in vivo studies [12–15]. Moreover, it can also be used to calculate the volume of renal calculi. The present study aimed to determine the effect of sodium bicarbonate-alkalized urine on renal calculus in patients with gout.

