#### Exclusion criteria

Potential subjects will be excluded if they meet any of the following:

(1) Allopurinol, probenecid, benzbromarone, and febuxostat tablets have been used for urate-lowering treatment (ULT) in the first 4 weeks of enrolment.

(2) Renal calculus >15 mm, obstruction (hydronephrosis), pain, and urinary tract infections requiring lithotripsy [10].

(3) Patients with secondary hyperuricemia caused by kidney disease, hematopathy, some medications, tumor chemoradiotherapy, and organ transplantation.

(4) Patients with a history of cardiocerebrovascular diseases, such as stroke, TIA, MI, and HF (NYHA II-IV), coronary artery surgery (for example, angioplasty, stent implantation, and bypass grafting).

(5) Patients with histories of peptic ulcer and gastrointestinal bleeding.

(6) Patients with active stage of liver disease and abnormal liver function or with a transaminase level of 1.2-fold higher than the upper limit of normal value.

(7) Patients with abnormal renal function and eGFR <30 mL/min.1.73 m^2^.

(8) Patients with malignant tumor or psychosis.

(9) Patients being allergic or intolerant to febuxostat.

(10) Patients with other (non-gout) chronic arthritis, acute inflammatory arthritis, and autoimmune diseases associated with arthritis.

(11) Patients who take or need azathioprine, mercaptopurine, theophylline, and cytotoxic chemotherapeutic drugs.

(12) Patients with a history of alcohol or drug dependence or need long-term daily painkillers for any reason.

(13) Patients who have been involved in other clinical investigations within the first 3 months of enrolment.

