#### Methods for additional analyses (e.g., subgroup analyses) {20b}

The hybrid control will use multivariate logistic regression, estimating the odds ratio (OR), and 95% confidence interval (CI). Clinically, significant variables in the univariate analysis will be included in the multivariate model. The goodness of fit will be evaluated by Hosmer–Lemeshow test. The statistical analysis was carried out using SPSS (version 26). A two-tailed significance level of 0.05 was used for all tests. *P*<0.05 indicated statistical significance.

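### The only hypertension outcome named is a yes/no incidence before and after treatment; it cannot register worsening in patients already hypertensive and is an insensitive measure of a harm the rationale names

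*Protocol article*

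**What the plan says.** Among the adverse events followed over 24 weeks, Outcomes {12}, Secondary outcomes, lists "the incidence of hypertension before and after treatment". No other hypertension outcome is named.

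Background and rationale {6a} explains why this harm matters: "alkaline urine may increase the risk of hypertension, water-sodium retention, and heart failure". It links these risks to a guideline's advice against starting alkalisation.

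The cardiovascular exclusion lists stroke, TIA, MI, heart failure (NYHA II–IV) and coronary procedures. It does not list hypertension. Intervention description {11a} provides for "concurrent treatment of concomitant hyperlipidemia, diabetes, hypertension, coronary heart disease, and cerebrovascular disease" in all subjects.

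Blood pressure itself is collected. Research procedures lists it among the vital signs, without dates. Secondary outcomes adds that "safety assessment will be conducted at baseline and at 24 weeks after treatment with respect to blood pressure" and other measures. Intervention description {11a} states that "the 1–12 weeks are double-blinded, and the 13–24 weeks are open-labeled".

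**The concern.** Incidence counts new cases among people at risk, so there is none before treatment. What can be recorded at baseline is the share who already have the condition.

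A patient who is hypertensive at entry is positive at both times. If bicarbonate raises that patient's pressure, or antihypertensive drugs are increased in response, the category does not change. The outcome can respond only through patients who cross from no to yes.

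The article says the trial will evaluate safety as well as efficacy. A hypertension result that shows little difference may be read as reassurance when the measure had little chance of showing one.

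**Working it through.** **1. The plan's own figure, to fix the numbers per arm.** Sample size {14} gives 89.74% against 64.10%, two-sided 0.05, 80% power, 1:1. With the pooled two-proportion formula, mean proportion 0.7692:

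n = [1.96·√(2·0.7692·0.2308) + 0.8416·√(0.8974·0.1026 + 0.6410·0.3590)]² / 0.2564² = (1.168 + 0.478)² / 0.0657 ≈ 41.2, so 42 per group.

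The stated 42 reproduces, and 42 × 1.15 = 48.3 gives the stated 49. The plan gives no figure for hypertension, so the checks below use 42 and 49 per arm.

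**2. Assumptions, none from the documents.** Systolic pressure in non-hypertensives is about N(124, 9), truncated below 140 mmHg. The 140 mmHg cut-off serves the illustration only. The SD of change is 10–12 mmHg, with 15 as a check for the continuous analysis. The true between-arm shift is 5 or 8 mmHg, and the share h hypertensive at entry is 30–70%.

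**3. Three ways to analyse the same data.**
- New onset among those at risk: two proportions q0 and q1 with n(1 − h) patients per arm.
- Share hypertensive after treatment: h + (1 − h)q0 against h + (1 − h)q1 with n per arm.
- Mean systolic change in everyone: power ≈ Φ(shift / (SD·√(2/n)) − 1.96).

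Example for the binary measures: n = 49, h = 0.3, SD 10, shift 5. Then q0 = 0.096 and q1 = 0.184, with about 34 at risk per arm, and new-onset power is 0.18. The shares after treatment are 0.368 and 0.429, with power 0.09.

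Example for mean change: n = 49, SD 12, shift 5. 12·√(2/49) = 2.42; 5/2.42 − 1.96 = 0.10; power 0.54.

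| Analysis (42–49 per arm) | 5 mmHg | 8 mmHg |
|---|---|---|
| Share hypertensive after treatment, h = 30–70% | 5–9% | 7–19% |
| New onset among those at risk, h = 30–70% | 8–18% | 15–39% |
| New onset, no hypertensives enrolled | 18–23% | 41–53% |
| Mean systolic change, SD 10–12 | 48–70% | 86–98% |
| Mean systolic change, SD 15 | 33–38% | 69–75% |

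**4. Reading the table.** With nobody hypertensive at entry, new-onset power is still only 18–23% for 5 mmHg, so much of the loss comes from dichotomising. Admitting hypertensive patients adds to it. Mean change is better throughout but not strong for small effects: for 3 mmHg its power is 15–32% over SD 10–15. Concurrent antihypertensive treatment would also blunt the mean change, which these figures do not model.

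**5. Timing.** The one dated post-baseline blood-pressure assessment is week 24. By then controls have had no placebo for 12 weeks and treatment is known. Retention {18b} sets a visit at week 12, the end of the blinded period, but the text does not tie blood pressure to it. The schedule figure is not shown and may do so.

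**The case against.** Three stronger readings are tempting, and the documents do not support them.

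*A real effect would be largely hidden.* Suppose new-onset hypertension is 10% on bicarbonate and 5% on placebo. With 20%, 40% or 60% hypertensive at entry, the shares after treatment are 28% vs 24%, 46% vs 43% and 64% vs 62%. A true ratio of 2.0 then looks like 1.17, 1.07 or 1.03. But this discards the baseline figure that the outcome also records. Subtracting it gives rises of 8 vs 4, 6 vs 3 and 4 vs 2 points, a ratio of 2.0 each time. Blood pressure itself is also assessed at baseline and week 24, and oedema is a separate outcome. Subtraction recovers new cases only; it still does not count worsening in patients already hypertensive.

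*The comparison is purely within arm.* The wording says when status is recorded, not which contrast is tested. The trial is randomised and placebo-controlled, and nothing says safety is compared only within an arm. Once arms are compared, febuxostat, diet, fluids and prophylaxis are common to both.

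*Hypertension is the main harm.* The rationale lists it first of three but does not rank them.

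It is also fair to say that thresholds, at-risk sets and rules for drug changes may stand in a fuller protocol or analysis plan. Their absence from an article is not the point. The point is the outcome as worded: a plan that followed it faithfully would use an insensitive measure.

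Finally, the cardiovascular exclusion is introduced by examples, so a reader might take hypertension as covered. Recording hypertension before treatment makes sense only if some patients have it at entry.

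**Conclusion.** The point holds as a matter of outcome definition. The named item calls a baseline prevalence an incidence, cannot register worsening or increased treatment in patients already hypertensive, and reduces a continuous measure to yes/no. Its only dated companion measurement falls in the open-label period.

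Under the stated assumptions, a 5 mmHg effect has at most about 18% power on either binary measure when 30–70% are hypertensive at entry, against 48–70% for mean systolic change at SD 10–12. These sizes are illustrative, because the article gives neither prevalence nor SD. The direction does not depend on the particular values tried.

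The claim stops there. The effect is not lost from the data, since blood pressure is recorded, and a between-arm comparison may well be intended.

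**What to change.** Replace the item with a between-arm comparison of change from baseline in systolic and diastolic pressure in all patients, at week 12 first (blinded) and week 24 second (open-label). Support it with between-arm counts of:
- new-onset hypertension among patients without it at baseline;
- worsened hypertension among patients with it, where starting or increasing antihypertensive treatment counts as worsening.

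The second count matters because treatment given in response to a rise would otherwise mask it in the mean change.

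Cost: revised outcome wording, one concomitant-medication field, and confirmation that blood pressure is taken at the existing week-12 visit. No new kind of measurement is needed. The new-onset count has a smaller denominator and low power on its own, so report it as supporting information and do not read a null result there as evidence of safety.
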